The tertiary outcome measures are:Grip strength will be evaluated using a JAMAR dynamometer according to the guidelines from the Swedish national quality register for hand surgery (HAKIR) [30]. The dynamometers used will be calibrated at least once every year.Active postoperative range of motion (ROM) for extension, flexion, pronation and supination will be evaluated using the HAKIR guidelines [30].Secondary dislocation and/or nonunion rate will be assessed with a lateral view radiograph 6 months after the operation. In order to minimize radiation dose, only one radiograph and one view will be obtained. If secondary dislocation and/or nonunion is found, the participant will be referred to the standard healthcare system, and further investigation may include a full radiographic examination. Any demonstrated secondary dislocation and/or nonunion is regarded as a complication.Sick leave related to the elbow injury, counted in days.Intra-operative fluoroscopy radiation level will be measured as the dose area product (DAP) in mGy·cm^2^, and intraoperative fluoroscopy time will be measured in seconds. This will be recorded at the time of surgery from the fluoroscopy machine used. The model and make of the machine vary between operating rooms and may change during the study.Surgical time will be recorded in minutes during surgery counting from skin incision to the final suture of the surgical wound.Post-operative antibiotic treatment is defined as any prescribed antibiotic treatment related to the surgery after the intervention.

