**Tertiary measures**										
ROM, flexion (degrees)	> 99%	> 99%	18	4.1	3.3	3.1	2.9	146^h^	7^h^	10^b^
ROM, extension (degrees)	> 99%	> 99%	10	2.9	2.4	2.2	2.1	− 3^h^	5^h^	10^b^
ROM, supination (degrees)	> 99%	> 99%	14	3.5	2.9	2.7	2.5	80^h^	6^h^	10^b^
ROM, pronation (degrees)	> 99%	> 99%	18	4.1	3.3	3.1	2.9	87^h^	7^h^	10^b^
Grip strength (newton)	43%	31%	352	9.4	7.6	7.2	6.6	32^i^	16^i^	5 ^j^
Post-operative antibiotics (yes/no)	< 1%	< 1%	6296	16%	13%	12%	11%	8%^a^	-	2%^b^
Secondary nonunion (yes/no)	< 1%	< 1%	9782	< 0.1%	< 0.1%	< 0.1%	< 0.1%	1%^k^	-	0.5%^b^
Sick leave (days)	< 1%^n^	< 1%^l^	30,790	18	14	13	12	35^b^	302	12
Fluoroscopy time (seconds)	< 1%	< 1%	3024	55	45	42	39	81^m^	94^m^	10^b^
Fluoroscopy DAP (mGy·cm^2^)	< 1%	< 1%	1492	19	16	15	14	25^m^	33^m^	5^b^
Operation time (minutes)	< 1%	< 1%	998	15	13	12	11	83^m^	27^m^	5^b^

Calculations of power and sample size requirements (n) for all outcome measures, including underlying assumptions. Previously published Minimally Clinically Important Differences (MCID) are given for outcomes where non-inferiority testing is performed and are used as non-inferiority margins in statistical analyses

^a^Based on a previous study at our institution [16]

^b^Based on estimations by the authors

^c^Based on QuickDASH following TBW [31]

^d^Based on unpublished data from a previous study where standard deviation (SD) was 22 for CF and TBW, although the sample was small

^e^Ranging from 3.5 to 19 points in the literature with a mean of 14 points [32–36]

^f^Based on outcomes following distal radius fractures as no elbow specific data was found in the literature [37]

^g^To our knowledge, no studies have reported MCID of SMFA following surgery for upper extremity injuries. The MCID was estimated to be half the standard deviation [38]

^h^Based on normal ROM [39]

^i^Based on data on elbow fractures [40]

^j^Based on a review of MCID of grip strength [41]

^k^Based on a study on the outcome of 196 olecranon fractures [42]

^l^Power if *n* = 100 and *n* = 85 as we expect half of the participant to work

^m^Based on data from all CF and TBW cases at our department during 2020

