### Follow-up

After surgery, follow-up will be identical in both study groups (Table 2). Standard peri-operative care will be given at the hospital.

**Table 2 Tab2:** Time-points for follow-up and data gathering, SPIRIT-figure

Activity	− 0.5 to 0	0	0.5	1.5	3	6	12	36
Inclusion, allocation, and randomization	x							
Intervention, both arms	x							
Primary outcome measures								
Reoperation rate				x	x		x	x
Secondary outcome measures								
Complication rate				x	x		x	x
Severe complication rate				x	x		x	x
QuickDASH				x	x		x	x
Patient satisfaction				x	x		x	x
Pain at rest				x	x		x	x
Pain in motion				x	x		x	x
SMFA		x					x	
Tertiary outcome measures								
ROM, flexion			x	x	x		x	x
Grip strength			x	x	x		x	x
Post-operative antibiotics				x	x		x	x
Secondary non union^a^			(x)	(x)	(x)	x	(x)	(x)
Sick leave				x	x		x	x
Fluoroscopy time		x						
Fluoroscopy DAP		x						
Operation time		x						

^a^The secondary dislocation or nonunion rate will be assessed from a lateral elbow radiograph at 6 months or will be recorded if diagnosed at any other time-point

In addition to descriptive baseline data, operation time, fluoroscopy DAP, and fluoroscopy time will be recorded. SMFA-questionnaires will be administered and collected by The Swedish Fracture Register (SFR) by mail shortly after the trauma (recall of pre-injury status), and 12 months later, and this data will be retrieved from SFR by the study officials.

At 2 weeks post-operatively, the cast will be removed, and a physiotherapist will record grip strength and ROM. Any reoperations, complications, ROM, grip strength, and return to work will be recorded at 6 weeks, 3 months, 12 months, and 36 months at the outpatient clinic at the dept. of Orthopaedics by a physiotherapist. PROMs (except SMFA) will be recorded by the participants in REDCap at the same time points. Reoperations and complications are recorded in each patient’s medical journal and subsequently retrieved by the study officials at interim analysis points and at the end of the trial.

At 6 months, a lateral view radiograph will be assessed by researchers DW and GC for any secondary dislocation or non-union. If secondary dislocation or nonunion is confirmed at any other point during the study, it will be recorded.

Any issue requiring additional follow-up or treatment will be handled in the standard health-care system which is public and tax-financed. After 36 months, the current follow-up will end.

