### Statistical analysis

For power and sample size calculations, the alpha value was set to 0.05. Our hypothesis is that CF will yield lower reoperation and complication rates, lower intra-operative radiation, and less intra-operative fluoroscopy time; thus, one-sided tests of proportions were used for sample size requirements calculations [47]. For all other variables, tests for non-inferiority were used with assumed means for ratio scalar and interval variables and assumed proportions for nominal variables [47].

Statistical power and sample size requirements for demonstrating clinically significant differences between the groups were calculated using minimal clinically important difference (MCID) values from the literature. Power and sample size data, including relevant assumptions for all calculations, are presented in Table 1.

We expect ≥ 80% power for reoperation rates, complication rates, severe complication rates, *Quick*DASH, SMFA, patient satisfaction, pain in motion and at rest, and ROM. However, we do not expect to achieve 80% power for analysis of grip strength, postoperative antibiotics use, secondary dislocation or nonunion rate, sick-leave time, fluoroscopy time, fluoroscopy DAP, or operation time (Table 1).

The minimal detectable differences (MDD) for various outcomes and study sizes are presented in Table 1. For some of the secondary and tertiary outcome measures, the MDD is smaller than the MCID meaning that the study is under-powered for proving non-inferiority between the groups. Early termination of the trial resulting in a smaller sample size would further reduce MDD, hampering the power of the study.

The final study groups consist of all participants that complete the follow-up and participants that withdraw but permit analysis; see the section “ Post-inclusion withdrawals and exclusions”. The study groups will be compared using the chi-squared test for categorical variables (reoperation, complication) and Student’s *t*-test for continuous variables.

Comparisons between the study groups will primarily be performed by “intention to treat” analyses. If large cross-over between study groups occurs, “as treated” analyses will be performed as well. Subgroup analysis stratified by Mayo classification, age, gender, open fracture, and high energy trauma is planned for all outcomes.

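### Grip strength is to be compared by an unadjusted t-test with no reference hand named, and its stated power follows an equivalence formula although non-inferiority is planned

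*Protocol article*

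**What the plan says.** Grip strength is listed among the tertiary outcomes under Objectives and outcome measures: "Grip strength will be evaluated using a JAMAR dynamometer according to the guidelines from the Swedish national quality register for hand surgery (HAKIR"). No side is named there or in the grip row of Table 2, and the HAKIR guideline is not reproduced.

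Under Follow-up, measurement starts at 2 weeks, when "the cast will be removed, and a physiotherapist will record grip strength and ROM". It is repeated at 6 weeks and at 3, 12 and 36 months, so there are five visits. Table 2 shows no grip measurement before the 2-week visit. Hand dominance is recorded, but only as a descriptive variable (Sample characteristics).

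Table 1 plans the outcome on a mean of 32, an SD of 16 and an MCID of 5: "Grip strength (newton) 43% 31% 352". Its note says that the MCIDs "are used as non-inferiority margins in statistical analyses". The Statistical analysis section gives the framework: "For all other variables, tests for non-inferiority were used with assumed means for ratio scalar and interval variables". It names Student's t-test, without covariates, for continuous variables, and it concedes that "we do not expect to achieve 80% power for analysis of grip strength". The Sample size section expects 170 participants for variables collected at follow-up, so the 31% figure is the one that applies.

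**The concern.** There are two linked problems.

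First, grip before the injury cannot be measured, and the planned comparison uses nothing in its place. An SD equal to half the mean, in adults of both sexes with no upper age limit, plausibly contains a good deal of ordinary variation between people. The patient's other hand is an obvious covariate for that variation. As written, the analysis would not use it even if it were measured.

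Second, the article tells readers that the grip question has a 31% to 43% chance of being answered. If those figures come from a different test than the one planned, the authors are conceding more than they need to, and the value of a cheap improvement is misjudged.

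At stake is the precision of one functional non-inferiority comparison. Under randomisation the unadjusted comparison is unbiased.

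**Working it through.** **Inputs.** From Table 1: SD 16, margin 5. From Statistical analysis: "For power and sample size calculations, the alpha value was set to 0.05". From Methods: 1:1 allocation, hence 100 per arm at 200 and 85 per arm at 170. A true difference of zero is assumed. The correlation rho between injured-hand and uninjured-hand grip is not in the documents, so a range is shown.

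**Step 1: reproduce the stated figures.** Equivalence by two one-sided tests, normal approximation:

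- n per arm = 2 × [16 × (1.645 + 1.282) / 5]² = 175.4, rounded up to 176, so 352 in total (stated: 352).
- Power = 2Φ(5/SE − 1.645) − 1, with SE = 16 × √(2/n).
- n = 100: SE = 2.263, power = 42.8% (stated: 43%).
- n = 85: SE = 2.454, power = 30.5% (stated: 31%).

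All three match. The SMFA and pain rows (138 needed, 94%, 89%) also reproduce with this formula, so it was not used for grip alone.

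**Step 2: the test that the article names.** Non-inferiority has one bound: power = Φ(5/SE − z).

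- One-sided alpha 0.05: 71.4% at 200 and 65.3% at 170. For 80%, n per arm = 2 × [16 × (1.645 + 0.842) / 5]² = 126.6, rounded up to 127, so 254 in total.
- One-sided alpha 0.025: 59.9% and 53.1%, with 322 needed.

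Neither gives 352.

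**Step 3: how much of the gap to 80% is the formula?** At alpha 0.05:

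- at 170: (65.3 − 30.5) / (80 − 30.5) = 34.8 / 49.5 = 70%
- at 200: (71.4 − 42.8) / (80 − 42.8) = 28.6 / 37.2 = 77%

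At alpha 0.025 the share is about 46% at either size (22.6/49.5 and 17.1/37.2).

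**Step 4: uninjured-hand grip as a covariate.** Residual SD = 16 × √(1 − rho²). The last column is a t-test on the plain side-to-side difference, with SD = 16 × √(2(1 − rho)) if both hands have the same SD.

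| rho | residual SD | non-inf. 0.05, N=200 | non-inf. 0.05, N=170 | non-inf. 0.025, N=170 | equivalence, N=170 | plain difference, non-inf. 0.05, N=170 |
|---|---|---|---|---|---|---|
| 0 | 16.00 | 71% | 65% | 53% | 31% | 42% |
| 0.3 | 15.26 | 75% | 69% | 57% | 38% | 53% |
| 0.5 | 13.86 | 82% | 76% | 65% | 52% | 65% |
| 0.6 | 12.80 | 87% | 82% | 72% | 63% | 74% |
| 0.7 | 11.43 | 93% | 89% | 81% | 77% | 84% |
| 0.8 | 9.60 | 98% | 96% | 92% | 92% | 94% |

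The adjusted model reaches 80% at 170 participants with rho of about 0.57 (non-inferiority, 0.05), 0.69 (non-inferiority, 0.025) or 0.72 (equivalence). At 200 the values are 0.46, 0.62 and 0.66.

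The plain difference gains nothing at rho 0.5 (its SD is again 16), loses power below that, and trails the adjusted model at every rho shown.

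**The case against.** The strongest reply is that the article never says only one hand is measured. It defers to a guideline that is not shown and may call for both hands, and a condensed article may omit that detail. This stands. A reader might infer that only the injured arm is measured, but the documents do not support it. The point about the analysis survives either way: the article itself fixes an unadjusted t-test and a raw SD, so even a measured second hand would go unused.

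A reader might also infer that the low power comes mainly from lacking a reference value. Step 3 contradicts this at one-sided 0.05, where 70% to 77% of the gap is the formula. Nor can one say that the other hand would restore most of the power. That depends on a correlation the documents do not give, and under the equivalence formula rho 0.5 yields only 52% at 170. The SD comes from elbow-fracture data, so injury and recovery may account for a substantial part of it. Age and sex, already collected, may explain some of the same variance.

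Extending the idea to range of motion has no power rationale, since Table 1 already states more than 99% for every direction.

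Finally, grip strength is tertiary, the sample size rests on reoperation, and the low power is openly declared. This limits the importance of the point but does not remove it, because the declared figures belong to a different test and the remedy is cheap.

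**Conclusion.** The point holds in limited form. The stated 43%, 31% and 352 are equivalence figures. Under the non-inferiority test that the article names, at one-sided 0.05, they should read about 71%, 65% and 254. That leaves about 15 percentage points to 80% at 170 participants, and adjustment for the uninjured hand could close that gap if rho is about 0.57 or higher. A smaller correlation still helps (69% at rho 0.3).

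This rests on the protocol's SD and margin, a true difference of zero, the normal approximation, an assumed rho that may differ between visits, and the premise that the fixation method does not affect grip in the other hand. If alpha is meant as 0.025 one-sided, the unadjusted figures are 60% and 53%, with 322 needed.

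No primary or secondary conclusion is affected. The loss is of precision, not validity. The change is worth making because it needs no extra patients or visits.

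**What to change.** 1. State whether grip is measured in both hands. If it is not, record the uninjured hand once, with the same device and procedure, at an existing visit. The 2-week visit is the earliest; participants already past it can be measured at a later one.
2. Replace the t-test for grip strength with a linear model of injured-side grip on treatment arm, uninjured-side grip and whether the injured side is dominant. Compare the confidence limit for the arm difference with the margin of 5. Do not use a plain side-to-side difference.
3. Recalculate the grip row of Table 1 with the non-inferiority formula, stating the one-sided alpha and the assumed between-hand correlation with a range. Check the other non-inferiority rows for the same formula.

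The cost is about two minutes and one data field per patient if the second hand is not yet measured, and otherwise only the analysis wording and the table. Patients with previous disease of the other arm give a poorer reference. That costs precision but does not bias the randomised comparison.

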### Null hypothesis

The null hypothesis in this study is that there is no difference in outcome measures at the follow-up time-points in adult participant with Mayo type 2a and 2b olecranon fractures treated with CF and TBW. Our alternative hypothesis is that CF yields superior results with fewer reoperations, fewer overall and severe complications, lower intra-operative radiation time and exposure, and non-inferior results in other outcomes.

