### Allocation and randomization

Prior to commencement of the study, a randomization sequence will be created by a research assistant using a tool provided by the US National Cancer Institute (NCI) [43]. The sequence will be created using maximally tolerated-imbalance (MTI) randomization and entered into the REDCap software [44, 45]. No one will be able to access the sequence once entered to into REDCap. Randomization will be stratified by age (≥ 65 years/ < 65 years), gender (male/female), and smoking (yes/no). These parameters are chosen as they are hypothesized to affect outcome and are available at inclusion.

Before the intervention, stratification data will be collected and the participant will be allocated to either intervention in the surgical ward just prior to when the patient enters the operating theatre by the steering committee using the sequence in the REDCap software, whereby a unique ID will be created for each participant.

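### The protocol warns that fluoroscopy machines differ between theatres and may change, yet compares dose area product with an unadjusted t-test: an avoidable loss of precision of unknown size, not a bias

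*Protocol article*

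**What the plan says.** Under *Objectives and outcome measures*, intra-operative DAP (mGy·cm²) and fluoroscopy time (seconds) are tertiary outcomes. On how they are obtained: "This will be recorded at the time of surgery from the fluoroscopy machine used". The next sentence is: "The model and make of the machine vary between operating rooms and may change during the study".

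Under *Null hypothesis*, the alternative includes "lower intra-operative radiation time and exposure" with cerclage fixation. This is a directional claim, kept apart from the outcomes for which only non-inferiority is sought.

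Under *Statistical analysis*, the arms are to be compared by chi-squared test for categorical variables and "Student’s *t*-test for continuous variables". No covariate or transformation is named.

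Under *Allocation and randomization*, the strata are age, gender and smoking. Machine, operating room and hospital site are not among them. Nor do they appear among the descriptive variables in *Sample characteristics* or the subgroups in *Statistical analysis*.

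Table 1 plans DAP with mean 25, SD 33 and a difference of 5 mGy·cm². Footnote m gives the source of the mean and SD: "Based on data from all CF and TBW cases at our department during 2020".

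**The concern.** The protocol identifies a source of measurement variation in one of its hypothesised outcomes and then names an analysis that ignores it. If machines of different make give different DAP for the same procedure, that difference adds to the spread within each arm and widens the confidence interval for the treatment difference. Recruitment is planned from January 2023 to 2027 at Malmö and Lund, so both differences between rooms and replacement of a machine during the trial are realistic.

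At stake is the precision of one tertiary comparison that the protocol already calls under-powered. The practical urgency is that the machine is easy to note at surgery and may be hard to recover years later.

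**Working it through.** **1. The plan's own figure.** Inputs from Table 1: SD 33, difference 5, total of 1492 for 80% power. The total is N = 4 × (m × SD / difference)².

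- With m = z0.95 + z0.90 = 2.926 (an equivalence-type multiplier): 4 × (2.926 × 33 / 5)² ≈ 1492. This reproduces Table 1. Rounding up per arm can add a patient or two.
- With the one-sided superiority multiplier z0.95 + z0.80 the total is 1078; with the two-sided multiplier it is 1368.

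Table 1's power below 1% at n = 200 also belongs to the equivalence-type formula. As a superiority comparison, power at 100 per arm is 28% one-sided or 19% two-sided. That mismatch is a separate matter. Here it only fixes the starting point.

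**2. Validity.** Simulation with allocation independent of machine, four machines, 200 patients and 10,000 trials per setting: when machines account for 10%, 30% and 50% of the variance, the unadjusted t-test has two-sided type I error of 4.7%, 4.8% and 5.2%. There is no inflation.

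**3. How much variance could be removed.** The protocol gives no between-machine figure, so this step is an assumption. Take two equally used machines whose mean DAPs have ratio f, with overall mean 25 and SD 33. The between-machine variance is 25² × ((f − 1)/(f + 1))², and its share is that value divided by 33² = 1089. The residual SD is 33 × √(1 − share), and SE = residual SD × √(2/100). Power for 5 mGy·cm² is Φ(5/SE − 1.96) two-sided or Φ(5/SE − 1.645) one-sided.

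| Ratio f | Between-machine variance | Share | Residual SD | SE | Power, two-sided | Power, one-sided |
|---|---|---|---|---|---|---|
| no adjustment | – | – | 33.0 | 4.667 | 18.7% | 28.3% |
| 1.5 | 25.0 | 2.3% | 32.6 | 4.613 | 19.1% | 28.7% |
| 2 | 69.4 | 6.4% | 31.9 | 4.516 | 19.7% | 29.5% |
| 3 | 156.3 | 14.3% | 30.5 | 4.319 | 21.1% | 31.3% |

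This uses only the mean and SD, with a normal approximation and a common SD in both arms.

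**4. Simulation with skewed data.** Assume log-normal DAP with log-SD √ln(1 + (33/25)²) = 1.004, two equally used machines, 100 per arm, two-sided 5%, and a treatment effect that multiplies DAP. Raw-scale power without and with a machine term:

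- True reduction of 5 mGy·cm² (5/25 = 20%): 25% to 27% at 2-fold; 26% to 30% at 3-fold.
- True reduction of 30% (7.5 mGy·cm², a value not in the protocol): 50% to 51% at 1.5-fold; 53% to 56% at 2-fold; 54% to 63% at 3-fold.

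Power here exceeds step 3 partly because a multiplicative effect also shrinks the SD in the cerclage arm. The gain from the machine term is about 0 to 9 points across these settings.

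**5. Can adjustment rescue the comparison?** If machines accounted for as much as 50% of the variance, the residual SD would be 33 × √0.5 = 23.3 and one-sided power for 5 mGy·cm² would be 45%. It stays well short of 80%.

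**The case against.** The strongest reply is that nothing here is an error. An unadjusted t-test in a randomised trial is valid, the machine limitation is disclosed, and the protocol says it does not expect 80% power for DAP. The outcome is tertiary and drives neither sample size nor stopping. A fuller analysis plan might add covariates. The planning SD comes from all 2020 cases, so it probably already contains between-machine variation. All of this stands and keeps the point small. It does not remove it: the protocol does name a test, the test sits badly with its own warning, and a better one costs almost nothing.

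Four stronger readings are tempting and are not supported.

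- *Bias.* A reader might infer that differing machines distort the comparison. Allocation is random, so machines balance in expectation, and step 2 shows correct type I error. A chance imbalance is already allowed for in the standard error.
- *A large loss of power.* Table 1's SD exceeds its mean, so a reader might infer that a log-scale analysis with a machine term would recover a great deal. At a 2-fold ratio most of such a gain comes from the transformation, not the machine term, and it rests on an assumed log-normal shape and a 30% effect. In a gamma check with the same mean and SD, the log-scale test does worse (25% against 46%). The protocol does not give the shape.
- *Fluoroscopy time.* The protocol does not say that machine type alters recorded seconds, so the point is confined to DAP.
- *Machine as a guaranteed pre-randomisation covariate.* Allocation takes place "in the surgical ward just prior to when the patient enters the operating theatre", but the protocol does not say that theatre or machine is fixed before it. If the choice of machine could follow allocation, adjustment would need care.

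**Conclusion.** The point holds as a minor one about precision. For DAP, part of a declared superiority hypothesis, the protocol recognises that instruments vary and leaves that variation in the error term. The unadjusted comparison is unbiased and keeps its type I error.

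The size of the loss is unknown. Under the stated assumptions (two equally used machines, log-normal DAP matched to Table 1, 100 per arm, two-sided 5%), a machine term alone is worth roughly 0 to 9 percentage points of power for ratios of 1.5 to 3. At 5 mGy·cm² it is worth 2 to 4 points for ratios of 2 to 3, and the comparison stays far below 80%. The machine ratio, the number of machines and how evenly they are used are all assumptions.

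**What to change.** - Record the fluoroscopy machine (make and model, or theatre) with each DAP reading.
- In *Statistical analysis*, replace the t-test for DAP with a regression on arm plus machine category, opening a new category whenever a machine is replaced.
- Keep the unadjusted comparison as a sensitivity analysis, in case the choice of machine follows allocation.
- If a transformation or log link is wanted, fix it in advance from the 2020 department data. That is a separate choice and not part of the fault described here.

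The cost is one extra data field and a slightly more complex analysis. No additional patients, visits or procedures are needed.
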